#### Plans to promote participant retention and complete follow-up {18b}

Patients will be contacted by phone when they do not complete the questionnaire at four weeks follow-up that captures the primary outcome within three days. The researcher will ask the patient to verbally rate the items that are necessary to evaluate the primary endpoint. In addition, the researcher will remind the patient to complete this questionnaire. Patients who fill out the questionnaires online will receive a reminder if they do not return the questionnaire within 1 week. Patients who fill out the questionnaires on paper will be called by the research team to keep them engaged. Other secondary outcomes are based on information from the medical health record and, therefore, this data will be near to complete.

Patients who withdraw from this trial will be followed up in the PRESENT cohort if they do not withdraw from the PRESENT cohort. PRESENT data can be used for outcome evaluation. If they withdraw from the PRESENT cohort, their data up to withdrawal will be retained and utilized in analysis.

#### Data management {19}

Demographic and clinical data will be collected in the electronic data capture system Castor (Amsterdam, The Netherlands, www.castoredc.com). The database includes multiple build-in skips and data validation checks to promote data quality, and an electronic audit trial log of all study event is stored. The data will be managed by a data manager and the research team will have access to the data. Access will be managed by authorization of accounts. PROMs will be sent out to the patients using PROFILES, which stands for Patient Reported Outcomes Following Initial treatment and Long term Evaluation of Survivorship (www.profielstudie.nl). Patients can complete the questionnaire on paper or online. Hardcopy questionnaires will be entered into PROFILES and physically stored in a secure archive of the study site. For other study files, a local secured research folder on the network drives of the study site will be used to be sure that only authorized personnel have access to the data.

#### Confidentiality {27}

The data will be handled confidentially and in compliance with the Dutch Personal Data Protection Act (De Wet Bescherming Persoonsgegevens). Research data will be coded by an identification number that will not be based on identifiable personal data. The subject identification code list to personal data will be only accessible to authorized personnel. Informed consent forms will be stored in a secure archive of the study site.

#### Plans for collection, laboratory evaluation, and storage of biological specimens for genetic or molecular analysis in this trial/future use {33}

Not applicable. No biological specimens will be collected.

### Statistical methods

#### Statistical methods for primary and secondary outcomes {20a}

The primary outcome is physical functioning 4 weeks after the start of the treatment, which will be expressed as a score on a 0–100 scale. First, we will calculate within-group changes from baseline to 4 weeks after the start of the treatment, which will be expressed as mean changes with corresponding 95% confidence intervals. Linear regression analysis or analysis of covariance (ANCOVA) following the intention-to-treat principle will be performed to compare the intervention arm with the control arm in terms of physical functioning, controlling for baseline physical functioning, age, Karnofsky performance score, and medication use. Differences between treatments and 95% confidence intervals will be calculated.

The proportion of patients in the intervention and control arm reporting a pain response will be compared by Fisher’s exact test or *χ*^2^ test.

Within-group changes in HRQOL from baseline to 4 and 8 weeks and 3 and 6 months will be expressed as mean change with corresponding 95% confidence intervals. We will assess between-group differences in HRQOL as a continuous outcome using linear regression analysis. The proportion of patients with a clinically relevant improvement or deterioration, i.e., an increase or decrease, respectively, of at least 10 points will be compared between the intervention and control arm at every time point by Fisher’s exact test or *χ*^2^ test [24, 28]. In addition, the proportion of patients reporting a clinically relevant improvement at any time point within 3 months will be compared.

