### Who will take informed consent? {26a}

Patients will be informed at the outpatient innovation clinic by the research team about the PRESENT cohort. Patients are asked informed consent for the collection of demographic and clinical data and patient-reported outcome measures (PROMs) at regular time points. Patients can provide additional consent for randomization into future intervention studies (i.e., broad consent) [11]. Patients who provided broad consent and who meet the eligibility criteria will be randomly allocated 1:1 to the intervention or control arm stratified by renal cell carcinoma versus other primary tumor histologies. Patients allocated to the intervention arm will be offered the intervention, which they may accept or refuse. Upon acceptance, informed consent will be obtained by a member of the research team.

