#### Sample size {14}

Four weeks after the start of treatment, patients in the control group may just have received radiotherapy or still need to undergo radiotherapy. Therefore, we assume that they do not experience a pain response yet at that time point. From the PRESENT cohort, we know that patients who did not experience a pain response after radiotherapy had a physical functioning mean score of 43.6, 4 weeks after the start of radiotherapy.

A recent study reported a minimal clinically important difference (MCID) of 13 points on the EORTC QLQ-C15-PAL physical functioning scale in patients with bone metastases undergoing radiotherapy [22]. To detect a 13 point difference with an 80% power, a two-sided *α* of 5% and standard deviation of 22, 45 patients are needed in each arm. We expect that 90% of the patients offered the intervention will accept the offer. To compensate for refusal, questionnaire nonresponse, and possible dropouts, we will increase the sample size by 10%, resulting in a total sample size of 100 patients.

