### Assignment of interventions: allocation

#### Sequence generation {16a}

A computer-generated allocation sequence will be created using random permuted blocks of patients. Randomization will be stratified by spinal metastases from renal cell carcinoma versus other histologies.

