#### Methods for additional analyses (e.g., subgroup analyses) {20b}

Not applicable. There will be no additional analyses (e.g., subgroup and adjusted analyses).

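### The primary ANCOVA omits the trial's only stratification factor, renal cell carcinoma versus other histologies; adding it is a free but minor improvement

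*Protocol article*

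**What the plan says.** **Randomisation.** Sequence generation {16a} of the protocol article specifies permuted blocks and adds: "Randomization will be stratified by spinal metastases from renal cell carcinoma versus other histologies". The consent section {26a} repeats it: "stratified by renal cell carcinoma versus other primary tumor histologies". No other stratification factor is named.

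**Primary model.** Statistical methods {20a} states: "Linear regression analysis or analysis of covariance (ANCOVA) following the intention-to-treat principle will be performed". The same sentence goes on to name the covariates of the model: "controlling for baseline physical functioning, age, Karnofsky performance score, and medication use". RCC status is not in the list, and no other section adds it to the model.

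**Additional analyses.** Section {20b} says: "There will be no additional analyses (e.g., subgroup and adjusted analyses".

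**Sample size.** Section {14} gives a figure per arm: "To detect a 13 point difference with an 80% power, a two-sided *α* of 5% and standard deviation of 22, 45 patients are needed". It then inflates that figure for refusal, nonresponse and dropout: "we will increase the sample size by 10%, resulting in a total sample size of 100 patients". This calculation uses no covariate and no stratum.

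**The concern.** Stratified blocks force the arms to be nearly balanced on histology. If histology predicts the outcome, that balance reduces the true sampling variance of the treatment difference. A model without the stratum does not register the reduction. Its standard error is computed as though histology could still differ between the arms by chance, so the interval is wider than the design warrants and the test rejects too rarely under the null.

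This is not a detail left open for a statistical analysis plan. The article sets out a covariate list, and the list does not match the article's own randomisation. What is at stake is some precision on the primary comparison and the agreement of analysis with design. The validity of the result is not at stake.

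**Working it through.** **Inputs from the protocol, section {14}:** difference 13 points, SD 22, two-sided α 5%, power 80%, 45 per arm.

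**Assumed inputs, not in the documents:** RCC share p and difference d in mean 4-week physical functioning between RCC and other histologies. The range shown is p = 10–25% and d = 5–15 points.

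**Step 1: reproduce the plan's figure.**
n per arm = 2(1.960 + 0.842)² × 22² / 13² = 44.96, rounded up to 45. Power at 45 is 80.0% by the normal approximation. A t-based calculation gives 79.2% at 45 and needs 46 for 80%. Inflation: 45 / 0.90 = 50 per arm, 100 in total. The stated figures reproduce.

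**Step 2: baseline precision.**
SE = 22 × √(2/45) = 4.64 points; 95% half-width = 1.96 × 4.64 = 9.09 points.

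**Step 3: effect of the omitted stratum.** Hold the total SD at 22 and treat the strata as exactly balanced.

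- Share of variance due to RCC: R² = p(1 − p)d² / 22²
- Reported SE divided by true SE: 1 / √(1 − R²)
- Actual α without the stratum: 2[1 − Φ(1.96 / √(1 − R²))]
- With true SE s = 4.64 × √(1 − R²), power without the stratum is Φ(13/s − 1.96/√(1 − R²)), and power with it is Φ(13/s − 1.96)

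| p | d | R² | SE overstated by | Actual α | Power without | Power with | Half-width reduced by (points) |
|---|---|---|---|---|---|---|---|
| 10% | 5 | 0.5% | 0.2% | 0.050 | 80.1% | 80.2% | 0.02 |
| 10% | 10 | 1.9% | 0.9% | 0.048 | 80.3% | 80.8% | 0.09 |
| 15% | 10 | 2.6% | 1.3% | 0.047 | 80.4% | 81.1% | 0.12 |
| 20% | 10 | 3.3% | 1.7% | 0.046 | 80.4% | 81.3% | 0.15 |
| 15% | 15 | 5.9% | 3.1% | 0.043 | 80.8% | 82.4% | 0.27 |
| 25% | 15 | 8.7% | 4.7% | 0.040 | 81.1% | 83.5% | 0.40 |

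Worked example, p = 15%, d = 10: R² = 0.15 × 0.85 × 100 / 484 = 0.0263. The half-width falls by 9.09 × (1 − √0.9737) = 0.12 points.

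**Step 4: simulation check.** Stratified blocks of 4 (block size assumed), 90 patients, 6,000 runs per scenario, Monte Carlo error about 0.003 on a 5% rejection rate.

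- p = 10%, d = 10: type I error 0.048 without the stratum and 0.050 with it; power 78.7% and 79.2%.
- p = 20%, d = 10: type I error 0.048 and 0.053; power 78.8% and 79.7%.
- p = 20%, d = 20, beyond the range above and run to make the mechanism visible: type I error 0.036 and 0.053; power 80.8% and 85.1%.

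The direction agrees with the formulas. At a 10-point difference the gap in type I error is close to simulation noise.

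**Step 5: what the table leaves out.** It uses the marginal SD and a raw RCC difference. The planned model already adjusts for baseline physical functioning, age, Karnofsky score and medication use. Only what RCC explains beyond these counts, and any overlap shrinks the gain.

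**The case against.** The strongest reply is that the planned analysis is already valid and the gain may be nil. The documents do not say why RCC was chosen as the stratum, and it may have little to do with physical functioning at 4 weeks. If so, nothing is lost by omitting it. Even at the top of the assumed range the interval narrows by 0.4 points on a 0–100 scale. All of this stands, and it is why the point is minor.

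It can also be said that {20a} never calls its list exhaustive, and that {20b} concerns additional analyses and does not define the primary model. That is fair: {20b} cannot be a ban on adjustment, because the primary model is itself adjusted. But an explicit list that leaves out the one stratifier, with nothing elsewhere to add it, is still a stated mismatch.

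A reader might infer more than the documents support:

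- **That the primary test is biased or anti-conservative.** It is neither. The error runs towards intervals that are too wide.
- **That the trial is short of power and cannot afford the loss.** The stated sample size reproduces, and it takes no credit for baseline adjustment. Whether refusal or dropout erodes power is a separate question, which this point does not settle.
- **That the secondary analyses are wrong for the same reason.** Section {20a} names no covariates for the between-group HRQOL regressions, so there is no stated list to contradict. The proportions "reporting a pain response will be compared by" Fisher's exact or χ² test are validly compared, if slightly conservatively. No size has been worked out for that endpoint.

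**Conclusion.** The mismatch is real: randomisation is stratified by RCC status and the stated primary model leaves it out. If RCC is prognostic beyond the four listed covariates, the reported standard error is slightly too large and the test slightly conservative. For assumed shares of 10–25% and differences of 5–15 points, R² runs from 0.5% to 8.7%, actual α from about 0.050 down to 0.040, and the power forgone from 0.1 to 2.4 points. At middle values (10–20%, 10 points) it is 0.5 to 0.9 points. These figures are upper estimates, because they ignore overlap with the other covariates, and they rest on shares and differences that the documents do not supply. The point is a free improvement of minor weight. It does not threaten the primary conclusion.

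**What to change.** In section {20a}, add RCC (yes/no) as a fixed covariate to the primary ANCOVA. Do this before outcomes are analysed: section {17a} says researchers cannot be blinded to allocation, so a term added after results are seen would look post hoc.

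The cost is one line of text and one degree of freedom. With 90 patients and a single coefficient per covariate, residual degrees of freedom go from 84 to 83, and the two-sided 5% critical value stays at 1.989. RCC status is already recorded, because it is needed to randomise. The planned total of 100 need not change.

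For consistency only, and optionally, the HRQOL models could carry the same term. If pain response is to be stratum-adjusted, a Mantel-Haenszel risk difference keeps the planned comparison of proportions, whereas logistic regression would move it to a conditional odds ratio.

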#### Outcomes {12}

The primary outcome is difference in physical functioning four weeks after the start of the treatment (i.e., surgery or radiotherapy) between the intervention and control arm, which will be measured with the European Organization for Research and Treatment of Cancer (EORTC) Quality of Life Questionnaire (QLQ) Core 15 Palliative Care (C15-PAL) [14].

Secondary outcomes include the following:Pain response at 2, 4, 6, and 8 weeks and 3 monthsDuration of pain relief as measured by the Brief Pain Inventory (BPI) [15, 16]Change in HRQOL as measured by the EORTC QLQ-C15-PAL and EORTC QLQ Bone Metastases 22 (BM22) from baseline to 4 and 8 weeks and 3 and 6 months [14, 17, 18]. For the present study, we will focus on overall QOL and the two functional scales (physical and emotional functioning) of the EORTC QLQ-C15-PAL, and the functional interference and psychosocial aspects domains of the EORTC QLQ-BM22 [17, 18]Duration of the hospital stay in daysDays until return to systemic oncological therapy, including hormonal, immune, targeted, and chemotherapyOccurrence of neurological deterioration, defined as deterioration of more than one grade on the American Spinal Cord Injury Association (ASIA) scale as measured by physical examination by a neurologists or trained ASIA physician [19, 20]Local control according to routine imaging and the electronic patient chartAEs, defined as any undesirable experience occurring to a patient during the study that may be related to the experimental treatment procedureProgression-free survival and overall survivalResource use, such as doctor visits, medication, hospital admissions, and surgical interventions, as well as out-of-pocket expenses such as for over-the-counter drugs and travel costs, will be recorded using the iMTA Medical Consumption Questionnaire (iMCQ) at 3 and 6 months [21]Cost-effectiveness

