### Data collection and management

#### Plans for assessment and collection of outcomes {18a}

According to the TwiCs design, demographic and clinical data and regular PROMs collected in the PRESENT cohort will be used for effect estimation. In general, patients fill out the EORTC QLQ-C15-PAL, the EORTC QLQ-BM22, the EuroQol (EQ) 5D-5L, and the BPI at baseline (upon cohort enrolment, i.e., before the start of treatment), 4 and 8 weeks, 3 and 6 months after initial treatment, and every 6 months thereafter. At 2 and 6 weeks, patients fill out an additional BPI [1, 14–18, 23]. Patients can choose to fill out the questionnaires on paper or online.

The primary outcome is physical functioning at 4 weeks that will be assessed using the EORTC QLQ-C15-PAL, a 15-item HRQOL questionnaire representing overall QOL, two functional scales (physical and emotional functioning), and six symptom scales (nausea, loss of appetite, dyspnea, constipation, sleeping difficulties, and fatigue) [14]. Secondary, change in HRQOL from baseline to 4 and 8 weeks and 3 and 6 months will be measured using the EORTC QLQ-C15 (overall QOL, physical and emotional functioning) and EORTC QLQ-BM22 (functional interference and psychosocial aspects). The EORTC QLQ-BM22 is a 22-item questionnaire representing four domains: painful sites, pain characteristic, functional interference, and psychosocial aspects [17, 18]. Items of the EORTC QLQ-C15 and -BM22 will be rated on a Likert scale ranging from 1 (not at all) to 4 (very much) with the exception of the overall QOL item that will be rated on a 7-point Likert scale ranging from 1 (very poor) to 7 (excellent). Scale scores will be linearly transformed to a 0–100 scale where a higher score on the overall QOL and functioning scales indicates better functioning, and on the symptom scales an increase of symptoms. The EORTC QLQ-C15 and -BM22 has been validated in patients with painful bone metastases or advanced cancer [17, 18, 24].

The duration of pain relief up to three months will be measured by the BPI which is a multidimensional tool to evaluate cancer pain [15, 16]. The BPI consists of eleven items representing two domains: pain perception and interference by pain. Items can be rated using a scale from 0 (no pain/interference) to 10 (maximum pain/interference). The BPI has been validated in patients with painful bone metastases [16]. Duration of pain relief will be defined as the time between response and progression or end of follow-up.

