#### Methods in analysis to handle protocol non-adherence and any statistical methods to handle missing data {20c}

Analysis will be based on the intention-to-treat principle. However, in accordance with the TwiCs design, patients who are selected for the intervention arm may refuse the intervention. In case of a high refusal rate (i.e., > 15%), we will also conduct a per protocol (PP) analysis including patients who completed the treatment as allocated. However, refusal may be selective, e.g., patients who are less physically fit may refuse the intervention. As a result, PP analysis may under- or overestimate the treatment effect. We will also perform a complier average causal effect (CACE) analysis to estimate the treatment effect among “compliers,” i.e., patients that accepted and received the intervention offered compared with hypothetical control patients who, if offered the intervention, would have accepted.

In the palliative oncology setting, questionnaire non-response is more likely due to inability to complete questionnaires as a result of for example fatigue and high distress or filling in questionnaires may be too burdensome. The proportion and patterns of missing data for the primary and secondary outcomes will be investigated. If needed, multiple imputation methods will be used to handle missing data under the assumption that data is missing at random. If the primary outcome data is determined to be missing not at random, a best–worst and worst-best case sensitivity analyses will be performed.

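### The HRQOL comparison between arms names no baseline adjustment, unlike the primary analysis, and so gives up precision that the collected baseline scores would provide

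*Protocol article*

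**What the plan says.** Outcomes {12} defines the secondary endpoint as "Change in HRQOL as measured by the EORTC QLQ-C15-PAL and EORTC QLQ Bone Metastases 22 (BM22) from baseline to 4 and 8 weeks", and further to 3 and 6 months. Five scales are singled out: overall quality of life, physical functioning and emotional functioning from the QLQ-C15-PAL, and functional interference and psychosocial aspects from the BM22. Plans for assessment and collection of outcomes {18a} has these questionnaires completed "at baseline (upon cohort enrolment, i.e., before the start of treatment), 4 and 8 weeks, 3 and 6 months after initial treatment".

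Statistical methods {20a} then treats the two endpoints differently:

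- Primary outcome: linear regression or ANCOVA, "controlling for baseline physical functioning, age, Karnofsky performance score, and medication use".
- HRQOL: "Within-group changes in HRQOL from baseline to 4 and 8 weeks and 3 and 6 months will be expressed as mean change" with 95% confidence intervals, and for the arms "We will assess between-group differences in HRQOL as a continuous outcome using linear regression analysis". No covariates and no repeated-measures structure are named.

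Methods for additional analyses {20b} adds: "There will be no additional analyses (e.g., subgroup and adjusted analyses". Sequence generation {16a} stratifies randomization by renal cell carcinoma versus other histologies.

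**The concern.** A covariate list stands in one paragraph and is absent two paragraphs later, for scales measured with the same questionnaires at the same baseline. An analyst following the text literally would fit arm alone. The contrast is sharpest for physical functioning at 4 weeks, which is the primary outcome and also one of the HRQOL scales and visits. It would be analysed once with the baseline score as covariate and once by a regression with none named, and the two arm differences could differ.

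At stake is precision. With about 50 patients per arm, chance differences at baseline are to be expected. Suppose the arms differ by D at baseline and the standard deviations at baseline and follow-up are equal. With correlation r, an unadjusted follow-up comparison then carries r × D of that difference into the estimate. A change-score comparison over-corrects by (1 − r) × D. Adjustment for baseline removes both.

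**Working it through.** **Inputs from the documents.** Sample size {14}: difference 13 points, SD 22, two-sided 5%, power 80%, 45 per arm, 100 in total. Statistical methods {20a}: 10 points as a clinically relevant HRQOL change.

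**Assumptions.** The correlation r between baseline and follow-up is not given; 0.3, 0.5 and 0.7 are used. SD 22 is stated for the primary outcome and is carried over to the HRQOL scales. Baseline and follow-up SDs are taken as equal.

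**The plan's own figure.** n per arm = 2 × (1.96 + 0.84)² × 22² / 13² = 45 after rounding up, and 90 / 0.90 = 100. Both reproduce.

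**Variance of the arm difference, relative to the unadjusted follow-up score.**

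- Follow-up score, unadjusted: 1
- Change score, unadjusted: 2(1 − r)
- Baseline as covariate: 1 − r²
- Hence covariate adjustment relative to change score: (1 − r²) / [2(1 − r)] = (1 + r) / 2

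| r | change score | baseline-adjusted | reduction vs follow-up score | reduction vs change score |
|---|---|---|---|---|
| 0.3 | 1.40 | 0.91 | 9% | 35% |
| 0.5 | 1.00 | 0.75 | 25% | 25% |
| 0.7 | 0.60 | 0.51 | 49% | 15% |

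At r = 0.5 the gain equals that from 1 / 0.75 = 1.33 times as many patients.

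**In points, with 45 per arm.** The standard error unadjusted is 22 × √(2/45) = 4.64, so the 95% CI half-width is 1.96 × 4.64 = 9.1. Multiplying by the square root of each variance ratio gives:

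| r | follow-up score | change score | baseline-adjusted |
|---|---|---|---|
| 0.3 | 9.1 | 10.8 | 8.7 |
| 0.5 | 9.1 | 9.1 | 7.9 |
| 0.7 | 9.1 | 7.0 | 6.5 |

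**Power for a 10-point arm difference**, from Φ(10/SE − 1.96): 57.8% for the unadjusted follow-up score, against 61.8%, 70.2% and 85.5% after adjustment at r = 0.3, 0.5 and 0.7. The 10 points are the protocol's threshold for change in an individual patient, used here only as a yardstick.

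Over this range adjustment is better than both alternatives. Which alternative the protocol intends changes the size of the gain, not its direction.

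**The case against.** The strongest reply is that this is a condensed article. Linear regression is also the method named for the adjusted primary analysis, so the term does not imply that covariates are absent, and the list for secondary outcomes may stand in an analysis plan that is not shown. The endpoint is moreover defined as change from baseline, so baseline probably enters through the change score. Part of this stands: the text is silent on HRQOL covariates and does not exclude them. But where the same section spells out covariates for one comparison and none for the next, the wording as published points to the weaker method. A change score does not remove the loss either, as the figures above show.

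Three stronger readings are tempting, and the documents do not support them.

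- A reader might infer that the HRQOL results rest on complete cases that shrink as patients die or stop answering. Section {20c} says otherwise: "The proportion and patterns of missing data for the primary and secondary outcomes will be investigated", with multiple imputation under missing at random if needed.
- A reader might infer a separate regression at each visit. The text says so only for the proportions with a 10-point change, not for the regression.
- A reader might take section {20b} as a ban on adjustment. It concerns analyses beyond those in {20a}, and the primary analysis in {20a} is itself adjusted, so it cannot be a general ban.

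It is also fair to say that allocation is randomized, so leaving out a baseline covariate costs precision without causing bias.

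**Conclusion.** The point holds as one of efficiency. The HRQOL comparison names no baseline covariate although the scores are collected and the primary analysis uses its own. For r between 0.3 and 0.7, adjustment would reduce the variance of the arm difference by 9% to 49% if follow-up scores are compared, or by 35% to 15% if changes are compared. These figures rest on the assumed correlation and on equal SDs at baseline and follow-up; the half-widths and power figures also rest on SD 22 applying to the HRQOL scales. Only a secondary outcome is affected. The primary conclusion and the sample size are not. This is a near-costless improvement rather than an error that endangers the trial.

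**What to change.** State in section {20a} that each HRQOL scale is compared between arms with adjustment for its own baseline score and for the renal cell carcinoma stratum. Preferably use one linear mixed model per scale for the scores at 4 and 8 weeks and 3 and 6 months, with arm, time, arm by time, baseline score and stratum, and an unstructured within-patient covariance. Report the arm difference with its 95% confidence interval at each visit. Add a clause to section {20b} making clear that it does not exclude this adjustment.

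The cost is wording, slightly more modelling work, and a simpler covariance structure named in advance in case the model does not converge. No new data are needed. The mixed model uses all observed visits under missing at random, the same assumption as the planned imputation. It does not resolve how deaths are handled in the HRQOL comparison and should not be presented as doing so.
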